However, a 3-h documentary requires significant investment both in terms of production costs and viewing time. Through this RCT, we will test whether a similar message to that promoted in the 3-h ‘Man Up’ documentary, encouraging men to seek help when they are experiencing mental health difficulties, can be effective when delivered through a much shorter video. In this RCT, we will test whether a 4-min video is similarly effective in promoting help-seeking among Australian men. If this video is shown to have no net negative effect on help-seeking, this video will be publicly released. The release of the video will be supported through a comprehensive media campaign aimed at promoting viewing of the video and for viewers to visit a purpose-designed website, which will house help-seeking and help-offering information, as well as other supporting videos and content.

Data assessing men’s help-seeking intentions, intentions to encourage other men to seek help, self-reliance, depression symptoms, and opinions regarding the allocated video will be collected across three timepoints: baseline (T1), post-intervention (T2—1 week after baseline), and 4-week follow-up (T3—4 weeks after T2). Participants will view the video between T1 and T2.

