### Sample size and power analysis

The sample size is calculated to detect a 0.25 standardised difference in mean on the GHSQ-Self score between the intervention and control group (90% power, 2-sided 5% significance level), assuming a correlation of 0.67 between T1 and T2 scores. This sample size of 446 participants also allows for 20% loss to follow-up. We have chosen a relatively small effect size given the universal nature of the intervention, where we would aim to create change by producing a small effect on a large number of men, and given that we are measuring intentions to seek help as the primary outcome, rather than actual help-seeking behaviour. Intentions was chosen over behaviour as the primary outcome given the small amount of time between T1 and T2 in which participants would have the opportunity to seek help as the need arose.

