### Statistical analyses

#### Primary outcomes

Analyses of continuous outcomes will be undertaken on an intent-to-treat basis, including all participants who have been randomised, regardless of their actual receipt of the intervention or withdrawal from the study. Mixed-model repeated measures (MMRM) analyses will be used because of the ability of this approach to include participants with missing data. The model will include factors of intervention arm, occasion of measurement (T1, T2), and their interaction. The effectiveness of the intervention will be assessed by a planned comparison of the difference between groups in change of the primary outcome variable from T1 to T2. An unstructured residual variance-covariance matrix will accommodate within-participant dependency. Tests of significance will use degrees of freedom adjusted using the Kenward-Roger method based on the observed information matrix. If necessary, transformation of the outcome variable will be undertaken to ensure distributional assumptions of the model are met.

Analysis of primary outcomes and some secondary outcomes will take place when all T2 post-intervention data have been collected, but before T3 follow-up data have been collected. This analysis will assess the effectiveness of the intervention from T1 to T2 on increasing participants’ intentions to seek help for mental health difficulties (primary outcome), and intentions to encourage other men to seek help and self-reliance (secondary outcomes).

At this time, we will assess whether there is evidence of a lack of net harm associated with viewing the intervention video. Doing this will allow us to inform the production company tasked with releasing the video into the public domain and promoting public access to the video whether they can release the film in the following month. This release will be dependent on the analysis of primary outcomes showing evidence of lack of net harm. Lack of net harm will be indicated by the lower confidence interval of the mean GHSQ-Self score in the intervention condition post intervention being no lower than that in the control condition, adjusting for any baseline differences. The parameters will be estimated within the framework of the models used to assess the effectiveness of the intervention (i.e. we will use an MMRM to obtain the estimated means and their confidence intervals).

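### The release rule compares per-arm confidence limits instead of the interval for the between-arm difference, so it reduces to a point estimate at or above zero with no prespecified error rate

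*Protocol article*

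**What the plan says.** The article's Background sets the policy: "If this video is shown to have no net negative effect on help-seeking, this video will be publicly released". The Dissemination section repeats it.

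Statistical analyses, Primary outcomes, makes it operational once T2 data are in and before T3: "This release will be dependent on the analysis of primary outcomes showing evidence of lack of net harm". The evidence required is "the lower confidence interval of the mean GHSQ-Self score in the intervention condition post intervention being no lower than that in the control condition", after adjustment for baseline differences. The section then says what the model will supply to the rule: "we will use an MMRM to obtain the estimated means and their confidence intervals".

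The same section assesses effectiveness differently, by a "planned comparison of the difference between groups in change of the primary outcome variable from T1 to T2". The interval that measures harm therefore comes out of the planned model, but the release rule does not use it. The article states no margin, confidence level or tolerated error for the rule.

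**The concern.** Harm here means a lower GHSQ-Self score with the intervention than with control. That is a difference between arms, and its uncertainty is the standard error of the difference. Setting one arm's limit against the other's does not use that standard error. If the two arm standard errors are about equal, they cancel and the confidence level plays no part.

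The decision has consequences. It opens a public media campaign, it is taken before follow-up data exist, and the article says there will be no separate data monitoring committee. The investigators also write that they want to be sure the video does no harm. A rule met by any non-negative point estimate does not show that, and it also stops half of the videos that do nothing.

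The words after the comparison are open to a second reading. The comparator could be the control arm's lower limit, which is the natural parse, or the control arm's mean. The two give very different release rates.

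**Working it through.** **Inputs.** Sample size section: target difference 0.25 SD, power 90%, two-sided α 5%, total 446, loss 20%, and for the correlation "assuming a correlation of 0.67 between T1 and T2 scores". Study design: 223 per arm. Analysed at T2: 223 × 0.8 = 178.4 per arm. Assumed: equal loss in the two arms and, where a level matters, 95% intervals. All effects are in SD units; θ is the true difference, intervention minus control.

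**The plan's own figure.** The release rule has no stated figure to reproduce. The sample size does reproduce from these inputs with a baseline-adjusted variance: n = 2(1 − 0.67²)((1.960 + 1.282)/0.25)² = 185.3 per arm; × 1.2 = 222.4, so 223 per arm and 446 in total. The inputs below are therefore the plan's.

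**Standard error of the difference.**
- T1-adjusted: √(2 × 0.5511/178.4) = 0.079.
- Difference in change from the MMRM with all randomised men: √(2 × [0.5511/178.4 + 0.33²/223]) = 0.085.

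**Limit against limit.** The rule is m_I − c·SE_I ≥ m_C − c·SE_C. With SE_I = SE_C the terms in c cancel, leaving D = m_I − m_C ≥ 0 for any c. So P(release) = Φ(θ/SE):

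| True difference θ | SE 0.079 | SE 0.085 |
|---|---|---|
| 0 | 50% | 50% |
| −0.05 | 26% | 28% |
| −0.10 | 10% | 12% |
| −0.20 | 0.6% | 0.9% |

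Simulation of 20,000 trials per scenario, with T1-adjusted arm means and 178 per arm, gives 50.1% at 0 and 10.5% at −0.10.

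When the rule is just met, D = 0 and the lower 95% limit of the difference is −1.96 × 0.079 = −0.15, or −1.96 × 0.085 = −0.17.

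**Intervention limit against control mean.** The rule becomes D ≥ 1.96 × SE_arm. With SE_arm = SE/√2, a neutral video passes with probability 1 − Φ(1.96/√2) = 1 − Φ(1.386) = 8.3%. The two readings differ by 50/8.3, about sixfold.

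**Rule on the difference with margin M.** Release if D − 1.96·SE > −M, so P(release) = Φ((θ + M)/SE − 1.96). With SE 0.079 (0.0786 unrounded):

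| M | θ = −M | θ = 0 | θ = −0.10 |
|---|---|---|---|
| 0.15 | 2.5% | 48% | 9% |
| 0.20 | 2.5% | 72% | 25% |
| 0.25 | 2.5% | 89% | 48% |

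With M = 0 the rule becomes the superiority test and releases a neutral video 2.5% of the time.

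**The case against.** The strongest reply is that the rule does guard against sizeable harm. Limit against limit, a video with true harm of 0.20 SD is released at most about 1% of the time. Passing excludes, at 95%, harm beyond about 0.15 to 0.17 SD, so the rule behaves like a non-inferiority test with a margin near 0.15 SD. That stands. A reader might infer that the rule gives no protection at all, and the figures do not support it. What remains is that nobody chose this margin: it equals 1.96 standard errors, so it widens as the data get weaker.

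A second reply is that a rule on the difference can be more lenient towards harm. That also stands. At a true harm of 0.10 SD, margins of 0.20 and 0.25 SD release the video 25% and 48% of the time, against 10–12% now. A reader might infer from the trial's precision that 0.20 to 0.25 SD is the right margin. Precision shows what can be tested, not what harm is tolerable.

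Three further inferences are tempting and should not be drawn:
- That the bar drops materially if control has more dropout or a larger SD. Retention of 90% in the intervention arm and 70% in control moves the cut-off on D by only 0.014 SD. The article describes one unstructured covariance matrix and does not say it is separate by arm.
- That the model cannot adjust for baseline. The planned change contrast removes T1 differences, and the article asks for adjustment. Raw T2 arm means would not do so, which is a reason to name the contrast in the rule.
- That the two readings differ tenfold. Using one standard error consistently, the ratio is about six.

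An analysis plan not shown may give a level or margin. It would still have to replace the comparison that the article states.

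**Conclusion.** The point holds as a fault in a stated decision rule. It is not a missing detail. On its natural reading, passing shows only that the adjusted point estimate is not negative, which falls short of the evidence the section promises. A neutral video, which the Background intends to release, is blocked half the time. A video harmful by 0.05 to 0.10 SD is released 10–28% of the time. On the other reading a neutral video is blocked about 92% of the time, so two analysts could reach opposite decisions from the same data.

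These figures rest on the plan's correlation, sample size and loss, equal loss by arm, and approximately normal estimates. The 50% depends only on near-equal arm standard errors.

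A reader might infer that the efficacy result is compromised. It is not: the primary test already uses the between-arm contrast.

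**What to change.** Replace the definition with: lack of net harm is shown if the lower limit of the two-sided 95% confidence interval for the T1-adjusted between-arm difference (intervention minus control) in T2 GHSQ-Self lies above −M. The planned difference-in-change contrast may serve in place of the T1-adjusted difference. Raw T2 arm means should not be used.

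The sponsor should justify M on substantive grounds, state it in scale points or SD units, and fix it before unblinding. The justification should show both columns of the trade-off, the release rate for a neutral video and for a harmful one. It should also note that 0.25 SD is the size of benefit the trial is powered to detect, so calling a harm of that size tolerable needs an argument. Word the conclusion as excluding a reduction in help-seeking intentions larger than M, since that is all the rule tests.

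The cost is one paragraph and no new data or model. The real burden is committing in advance to a margin, and accepting that a small M blocks many neutral videos while a large M lets more mildly harmful ones through.

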#### Secondary outcomes

Analyses of other outcome variables will follow the same methods as the primary outcome. Secondary outcomes will also include change in the primary and other outcome variables from baseline (T1) to follow-up (T3).

#### Subsidiary analyses

Subsidiary analyses will be undertaken to examine potential moderators of effectiveness and outcomes in subgroups. These subgroups will be defined by age group, English spoken at home vs other language spoken at home, and number of viewings of the video. These analyses will add the potential moderator variable as a factor to the model used in the main analyses. Incremental models will evaluate its significance as a stable and as a time-varying covariate and fit a three-way interaction of the moderator with group assignment and occasion of measurement. Comparisons within the latter interaction will address whether change over time differs significantly between intervention arms within subgroups and whether such differential changes differ significantly between subgroups. Additional exploratory analyses may be conducted with additional variables including self-reliance scores on the CMNI-30-SR and depression scores on the MDRS-7.

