### Participant selection

When participants register their initial interest in participating in the RCT via a registration website, they will be sent a detailed Plain Language Statement (PLS) outlining the requirements of trial participation. They must then attend an online orientation session run by one of our researchers and a study psychologist. In these sessions, the researcher will reiterate key background information from the PLS and answer questions to allow participants to provide informed consent. Once participants have had their questions answered, they will complete an online consent form, ticking a box to provide consent to continue to the T1 questionnaire (note that this includes consent to use of de-identified data for additional studies with ethical approval). If they do not consent, they will not proceed to the T1 questionnaire. The Depression Symptom Inventory—Suicidality Subscale (DSI-SS) [12] suicide risk screening questionnaire will be included in the T1 questionnaire. The study psychologist who attends the session will phone any participant who scores 2 or above on the DSI-SS to further assess their risk and to assist the participant in seeking further mental health support if the participant would like it. If the psychologist determines that the participant is at imminent risk of suicide or could be harmed by further participation, they will be excluded from further participation and referred for mental health support. If the participant is not determined to be at risk of harm, they will continue in the trial, but may still be referred for further support as required. The study psychologist will conduct a risk assessment using criteria such as whether the person has a current plan for suicide, and whether they have a history of suicide attempt. Participants will also be supplied with the psychologist’s contact details and able to contact them directly for further support for up to 4 weeks following completion of the T3 questionnaire. Following completion of the T1 questionnaire, participants will be randomised to view the intervention or control video.

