#### Treatment adherence

On day 3 after T1, participants will be encouraged via an email reminder including a personalised video link to watch the video. These links will provide participants with unlimited access to their allocated video until the completion of the T2 questionnaire. Participants will be sent the video link again with the link to complete the T2 questionnaire at day 7 after T1. To assess adherence to the intervention, we will record participants’ viewing behaviour related to the intervention and control videos by counting how many times the given video was started, how many times it was watched from beginning to end, when the video was paused, the number of times the participant tried to navigate away from the video page (e.g. by closing the tab or browser) and at what time points in the video the participant left the video page (e.g. 14 s). We will also ask one ‘attention’ question related to the content of the intervention or control video at T2. This is a question the participant can only answer by having attentively watched the video.

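### Number of video viewings is a self-chosen behaviour after randomisation, yet the plan uses it as a subgroup and moderator on the same footing as age group and home language

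*Protocol article*

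**What the plan says.** The Subsidiary analyses section sets out its aim as follows: "Subsidiary analyses will be undertaken to examine potential moderators of effectiveness and outcomes in subgroups". It then names three variables: "These subgroups will be defined by age group, English spoken at home vs other language spoken at home, and number of viewings of the video". All three get the same treatment. Each is added to the main model as a factor, and the final step is to "fit a three-way interaction of the moderator with group assignment and occasion of measurement". The contrasts to be read from that model are "whether change over time differs significantly between intervention arms within subgroups and whether such differential changes differ significantly between subgroups".

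The timing is given elsewhere in the protocol article:

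- Participant selection: "Following completion of the T1 questionnaire, participants will be randomised to view the intervention or control video".
- Background: "Participants will view the video between T1 and T2".
- Treatment adherence: "These links will provide participants with unlimited access to their allocated video until the completion of the T2 questionnaire". The same section says that viewing is logged in both arms as a measure of adherence.

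The Intervention and Control sections describe the two videos. One is a song by a large group of men about talking to others in difficulty. The other is an extract from a documentary about table tennis and cognitive processing speed.

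**The concern.** A subgroup comparison in a randomised trial is fair because the stratum was fixed before allocation, so each stratum is a small randomised trial of its own. That holds for age group and home language. It does not hold for viewing count, which arises after allocation and may be a response to the allocated video. Men who replay the song need not be the counterparts of men who replay the table-tennis extract.

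The analysis of change from baseline does not remove the problem. Bias arises whenever the reason for replaying also predicts change.

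At stake is whether the viewing-count results can be interpreted. A difference between arms among repeat viewers, or a significant three-way interaction, could look like a dose-response when the video has done nothing.

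**Working it through.** **Design inputs (Sample size and power analysis; Study design).** Effect 0.25 SD, 90% power, two-sided 5%, T1-T2 correlation 0.67, 223 per arm, 20% loss. The plan's own size reproduces with a baseline-adjusted variance: n = 2 × (1.960 + 1.282)² × (1 − 0.67²) / 0.25² = 185.3, so 186 per arm, and 186 × 1.2 = 223. No design figure is disputed here. The figures serve only to set the scale: 223 × 0.8 ≈ 178 completers per arm, and a change-score SD of √[2(1 − 0.67)] = √0.66 = 0.812, in units of the score SD.

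**Assumed inputs (not in the documents).** Viewing is driven by a latent normal variable, and a man counts as a repeat viewer (2+ viewings) when it exceeds 0.3, which is about 38% of men. Its correlation r with change in score is varied by arm. The true effect is zero for everyone.

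**Closed form for a link in the intervention arm only.** The mean of a standard normal above 0.3 is 0.3814 / 0.3821 = 0.998; below 0.3 it is −0.3814 / 0.6179 = −0.617. The spurious difference between arms is then:

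- repeat viewers: r × 0.812 × 0.998. For r = 0.1, 0.2, 0.3 this is 0.08, 0.16, 0.24 SD.
- the others: −r × 0.812 × 0.617. For the same r this is −0.05, −0.10, −0.15 SD.

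**Simulation.** 4,000 runs per row; change score regressed on arm, stratum and their product. With two occasions and complete data, this product corresponds to the planned three-way term. The Monte Carlo error at 5% is √(0.05 × 0.95 / 4000) ≈ 0.3 percentage points.

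| Viewing-change link | Difference, 2+ viewers (SD) | Difference, others (SD) | Test within 2+ rejects | Three-way test rejects |
|---|---|---|---|---|
| None | 0.00 | 0.00 | 6% | 5% |
| 0.2 in both arms, same frequency | 0.00 | 0.00 | 5% | 5% |
| 0.1, intervention only | +0.08 | −0.05 | 9% | 11% |
| 0.2, intervention only | +0.16 | −0.10 | 21% | 32% |
| 0.3, intervention only | +0.24 | −0.15 | 43% | 62% |
| 0.3 in both arms, more viewing in intervention | −0.09 | −0.10 | 11% | 5% |

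The simulated differences agree with the closed form. The intention-to-treat comparison rejects between 4.5% and 5.5% of the time in every row.

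**A second set of assumptions.** Here 30% are repeat viewers, and a trait correlates 0.3 with change and 0.5 with replay in the intervention arm. If the trait-replay correlation in the control arm is 0, the spurious difference is 0.14 SD and the tests reject 15% (subgroup) and 19% (interaction). Raising the control-arm correlation through 0.1, 0.2, 0.3 and 0.4 to 0.5 lowers the difference through 0.12, 0.09, 0.05 and 0.03 to 0.00 SD, and both tests return to 5%.

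**The case against.** The strongest reply is that differential viewing is not documented. The protocol contains no viewing data, and the design makes exposure alike in several respects. The Control section notes that the clips match in length, are both Australian and feature only men. Links and reminders go out on the same days in both arms. Participants are not told until T3 that two videos exist. All of this stands: that viewing differs by video is a reasonable inference from very different content and free re-viewing, not a fact in the document.

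It also stands that bias is conditional. With the same frequency and the same link in both arms there is none. With the same link but unequal frequency, the interaction test keeps its size and the within-stratum bias in the simulated case runs against the intervention.

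Finally, these analyses are labelled subsidiary, and the moderators are called potential ones. That limits the weight of the point but does not answer it. The section draws no distinction between viewings and the two baseline variables. The word exploratory appears only with additional variables, such as the self-reliance and depression scores.

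A reader might also infer that a false finding in repeat viewers would drive the video's release or the campaign's message. The document does not support that. Under Statistical analyses, Primary outcomes, release depends on the lack-of-net-harm assessment of the primary outcome, and no passage ties the subsidiary analyses to release or campaign content.

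**Conclusion.** The point holds in a conditional form. The plan lists a self-chosen, post-randomisation behaviour as a moderator beside baseline variables and reads contrasts between arms within its strata. Those contrasts are biased if viewing frequency or the viewing-outcome link differs by arm, and the interaction test is inflated if the link differs.

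The size cannot be derived from the document. Under the assumptions shown, the spurious difference among repeat viewers runs from 0 to about 0.24 SD, against a design effect of 0.25 SD, and interaction rejection runs from 5% to about 62%. The upper end needs a correlation of 0.3 in one arm and none in the other, so it should not be read as the expected value.

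It would go too far to say that these contrasts can have no causal meaning, or that a false dose-response will appear. They lack a causal reading only without further, untestable assumptions. The primary intention-to-treat analysis includes every randomised man whether or not he watched, and is unaffected.

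**What to change.** In Subsidiary analyses, delete number of viewings from the subgroup and moderator list and keep age group and home language. Report viewing counts by arm as adherence, which is the purpose given for logging them. Label any association between viewing and outcome as non-randomised and exploratory.

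Optionally, add a complier-average effect of receipt, with randomisation as the instrument and receipt taken from the player logs. It should state its exclusion restriction and how partial viewing is handled, since a man who leaves late in the video would be coded as unexposed although he saw most of it. This estimates the effect of receiving the video; it does not answer the question about number of viewings.

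The cost is a change of wording in the protocol, and in the analysis plan if it repeats the text, plus one model on logged data if the option is taken. The sample size stays at 446. What is lost is the viewing-count moderator result.

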**Fig. 1 Fig1:**
[figure not shown]
Timeline for the trial. *Note:* DSI-SS, Depression Symptom Inventory—Suicidality Subscale [12]. See Table 1 for further information about T1, T2, and T3 questionnaires and timing

**Table 1 Tab1:** Schedule of assessments

Variable	Measure	Timeline		
		T1	T2	T3
*Screening measure*				
Suicide risk	Depression Symptom Inventory—Suicidality Subscale [12]	X		
*Primary outcome measure*				
Help-seeking intentions	General Help-Seeking Questionnaire—Self [13]	X	X	X
*Secondary outcome measures*				
Intentions to encourage other males to seek help	General Help-Seeking Questionnaire—Other [13]	X	X	X
Self-reliance	Conformity to Masculine Norms Inventory 30—Self-reliance subscale [14]	X	X	X
Male depression symptoms	Male Depression Risk Scale-7 [15]	X		X
Health service use	Health Service Use Questionnaire	X		X
*Other measures*				
Socio-demographics	Information about age, postcode, country of birth, language, marital status, current student, highest education, and employment	X		
Social support question	Information about the number of close friends and close relatives	X	X	X
Feedback on video	Information about video enjoyment, likeability, take-home message, degree of intended sharing with others, and belief about impact		X	
Effects of viewing the video	Information about life changes and time spent with friends			X

*Note.* T1, the T1 questionnaire is completed in the online information session; T2, the T2 questionnaire becomes available 7 days after completion of the T1 questionnaire and the survey expires after 1 week; T3, the T3 questionnaire is made available 4 weeks after the T2 questionnaire is completed or expires. The survey link expires after 1 week

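### Age moderation is tested only in age groups entered as a factor, which loses power if the effect changes smoothly with age

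*Protocol article*

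**What the plan says.** The Subsidiary analyses section names three moderators. For the first it says: "These subgroups will be defined by age group". The other two are the language used at home (English or another) and how often the video was viewed. On how they enter the model it says: "These analyses will add the potential moderator variable as a factor to the model used in the main analyses". The models are then built up to "fit a three-way interaction of the moderator with group assignment and occasion of measurement", and comparisons within that interaction address both the arm difference inside each subgroup and whether that difference varies between subgroups.

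Table 1 lists the T1 socio-demographic items as "Information about age, postcode, country of birth, language, marital status, current student, highest education, and employment". It does not give the response format for age. Eligibility starts at 18 years with no upper limit.

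The Sample size and power analysis section sets the trial size for the overall comparison only, to "detect a 0.25 standardised difference in mean on the GHSQ-Self score between the intervention and control group (90% power, 2-sided 5% significance level". Scores on the two occasions are taken to correlate at 0.67. On attrition the section says: "This sample size of 446 participants also allows for 20% loss to follow-up". No power is given for any interaction. The Subsidiary analyses section plans no continuous-age moderation test and gives no reason for grouping.

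**The concern.** Of the three named moderators, language at home is a two-way split as the article defines it; age is not. Grouping treats all men within a band as the same age, so differences in age within a band contribute nothing to the test. With three or more groups the factor also uses more degrees of freedom than a single slope. The result can then depend on where the cuts fall.

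What is at stake is limited. The video is meant for public release with a media campaign, so whether its effect varies with age is useful to know. A non-significant grouped test could be read as showing no such variation when the test had little chance of finding it.

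**Working it through.** **Inputs from the protocol article.** Standardised difference 0.25, 90% power, two-sided 5%, T1–T2 correlation 0.67, 446 randomised 1:1, 20% loss. Completers: 446 × 0.8 = 356.8, about 357.

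**Step 1: the stated sample size.** n per arm = 2v(1.960 + 1.282)² / 0.25², with v the outcome variance in SD² units.
- Baseline-adjusted (ANCOVA) variance, v = 1 − 0.67² = 0.551: n = 185.3, so 186. Then 186 × 1.2 = 223.2, which matches 223 per arm and 446 in total.
- Change-score variance, v = 2(1 − 0.67) = 0.66: n = 221.9, so 222 per arm before any dropout allowance.

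The planned model has T1 and T2 as outcomes with an arm by occasion interaction, which is closer to the second variance. Both are carried forward.

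**Step 2: how weak an interaction test is at this size.** For two equal subgroups whose arm effects differ by d, the standard error of the difference is √(16v/N) and power is about Φ(d/SE − 1.96). With d = 0.25:

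| N | v | SE | d/SE | Power |
|---|---|---|---|---|
| 446 | 0.551 | 0.141 | 1.78 | 43% |
| 446 | 0.66 | 0.154 | 1.62 | 37% |
| 357 | 0.551 | 0.157 | 1.59 | 36% |
| 357 | 0.66 | 0.172 | 1.45 | 31% |

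A subgroup difference as large as the whole design effect would be missed more often than found.

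**Step 3: illustration of the loss from grouping.** Assumptions not in the article: moderation linear in age, age uniform, k equal groups, and a continuous-age test with 80% power.
- Non-centrality for 80% power on 1 df: (1.960 + 0.842)² = 7.85.
- Share of age variance kept by k equal groups: 1 − 1/k².
- Grouped test: non-centrality 7.85 × share, on k − 1 df.

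| Groups | Share kept | Non-centrality | df | Power |
|---|---|---|---|---|
| continuous | 1 | 7.85 | 1 | 80% |
| 2 | 0.750 | 5.89 | 1 | 68% |
| 3 | 0.889 | 6.98 | 2 | 65% |
| 4 | 0.9375 | 7.36 | 3 | 61% |

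With two groups the whole loss is discarded information. With three or four, the extra degrees of freedom outweigh the information recovered.

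**Step 4: the range on the trial's own N and correlation.** Non-centrality = N × 0.25 × b² × share / v, where b is the change in arm effect per SD of age, tested with a non-central F. Groups run from two to five, and age is taken as normal, uniform or right-skewed. The share kept is 0.53 to 0.75 with two groups and 0.69 to 0.89 with three.

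| N | v | b | Continuous | Grouped |
|---|---|---|---|---|
| 446 | 0.66 | 0.25 | 90% | 64–80% |
| 446 | 0.551 | 0.25 | 94% | 73–87% |
| 446 | 0.66 | 0.125 | 37% | 18–29% |
| 357 | 0.66 | 0.25 | 83% | 53–71% |
| 357 | 0.66 | 0.125 | 31% | 15–24% |

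**Step 5: where the direction reverses.** Suppose the effect steps at the median, the cut is at the median, and age is normal. Linear age then keeps 2/π = 0.64 of the information. With N = 446, v = 0.66 and effects shifted by ±0.25 SD on either side, the grouped test has 90% power and the linear one 73%.

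**The case against.** The section asks for more than a moderation test. It also wants arm comparisons within subgroups, and those need groups. This stands, so the planned contrasts should be kept and not replaced.

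This is a condensed article, and the number of groups, the cut-points and the modelling detail may properly sit in the analysis plan. That is also right, and a reader should not infer that missing cut-points are a fault. The point rests on what the article does state, grouped age entered as a factor, which any choice of cut-points inherits. The section also speaks of evaluating the moderator as a stable and as a time-varying covariate, but that does not change the stated definition of the age moderator as a group.

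Table 1 does not show that age is held in years. If only bands were collected, the point falls.

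A reader might infer that grouping always loses power, or always costs degrees of freedom. Neither holds. Two groups use one degree of freedom, as a slope does, and a step at the cut-point favours grouping. A purely linear term could also miss a U-shaped pattern.

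Nor would continuous age rescue the test: with b = 0.125 and 357 completers, at v = 0.66, power is 31% against 15–24%, inadequate either way. The 80% starting point in the illustration is a reference value and not a claim about this trial.

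**Conclusion.** The point holds as a minor matter of efficiency. The article fixes a grouped, factor-coded test of age moderation and plans no continuous alternative. Under roughly linear moderation, grouping takes 12, 15 and 19 percentage points off a test with 80% power (two, three and four equal groups, uniform age). On the trial's own N and correlation the loss in the scenarios above runs from about 6 to 30 points. These sizes rest on the shape of the moderation, the age distribution, equal groups and age being recorded in years, none of which the article gives.

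A reader might go further and take this as an error that weakens the trial's main result or the decision to release the video. The article does not support that. The analysis is subsidiary, and release depends on the overall GHSQ-Self comparison. No primary or secondary conclusion changes.

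**What to change.** Confirm that age is recorded in years. If so, add one sentence to Subsidiary analyses: the main test of moderation by age is the arm by occasion by continuous-age interaction, with a restricted cubic spline in age as a check for non-linearity. Keep the age-group contrasts already planned, for within-subgroup estimates and display.

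The change needs no new data if age is in years, and the primary analysis is unaffected. Its downside is that the main test assumes a roughly smooth, monotone age trend and would lose to grouping if the effect stepped at a cut-point. The spline check spends extra degrees of freedom (with three or four knots, two or three in all for age, as many as three or four groups), and its knots also have to be chosen. Power will remain low for modest differences, so a non-significant result should not be reported as evidence that the effect is the same at all ages.
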